## 4. Discussion

113 Suicide Prevention has the ambition to implement SUPRANET nationwide. The results of this study will help other regions to more effectively tailor the program to their context, important for the national implementation of the EAAD in The Netherlands. The results will be of high relevance for countries in and outside of Europe.

As suicides have been rising since 2007 in The Netherlands, 113 Suicide Prevention believes it is time to really tackle the problem, and directly target suicidal behaviour. While the focus of the public awareness campaign of the EAAD lies on depression, with the secondary aim to reduce suicidal behaviour, in SUPRANET we decided to directly focus on suicide. We believe the specific focus fits well in the Dutch culture, since the Dutch expect others to be open and direct. Furthermore, general practitioners and gatekeepers in The Netherlands are confronted with suicidal behaviour more often than before. Therefore, they understand the need for an intervention with a specific focus on suicide prevention. Regarding the public awareness campaign, we know from the literature that properly communicating about suicide can actually result in less suicidal behaviour (Papageno effect). 113 Suicide Prevention appoints to the subject suicide direct and encourages people to talk about it. Still, as it is a novum to offer a public campaign on suicide prevention in The Netherlands, a safety procedure is built in. As soon as any rise in adverse events are reported, either via the national railways or via other monitors, such as social media, the campaign will immediately be aborted.

Compared to existing studies on the EAAD, our study has a strong focus on change in recognition and treatment of suicidal behaviour in Dutch primary care. Since GPs play a crucial role in Dutch mental health care and in our suicide prevention intervention, and because the NIVEL primary care database provides good research opportunities in terms of reliable data collection, our project provides a unique chance to assess the effectiveness of the program within primary care. Ideally, we would also be able to collect data from other health care partners, such as social community teams or specialized (mental) health care. However, the results will offer unique insight in the way GPs deal with suicidal ideation and behaviour in depressed patients and will learn how to optimize the training of GPs. Additionally, once the NIVEL depression module has been constructed, it can be used for a longer period of time with only limited funding, allowing us to assess changes in suicide prevention within primary care over years to come.

Regarding the qualitative analysis, previous studies have done quite a large amount of work analysing the success and barrier factors of the EAAD program. Still, no overall list of success and barriers factors has been published. By doing so, our study hopes to facilitate the further implementation of the EAAD across Europe and beyond.

## 5. Conclusions

This paper describes the implementation of the European Alliance against Depression (EAAD) by creating local Suicide Prevention Action Networks (SUPRANET) in seven Dutch pilot regions and how we plan to evaluate it. The evaluation consists of both quantitative and qualitative analyses. The findings will be used (1) to facilitate the national implementation of EAAD in The Netherlands; and (2) to add new findings to the existing literature on EAAD.

## Figures and Tables

**Figure 1 ijerph-14-00349-f001:**
[figure not shown]
The 7 SUPRANET communities. Colouring represents the population density of the region.

**Figure 2 ijerph-14-00349-f002:**
[figure not shown]
The four level approach of SUPRANET Community, based on the European Alliance against Depression (EAAD).

**Table 1 ijerph-14-00349-t001:** Outcomes and measurements per target group.

Evaluation	Target Group	Compared to Baseline and to National Level, Does Being a SUPRANET Community Have an Impact on:	Measurement	Source
Part 1	General Public	Severity of suicidal ideation and behaviour	Suicide trends	Statistics Netherlands
			Suicidal Ideation Attributes Scale [15]	Online Survey 113
		Psychological distress	Kessler Psychological Distress Scale (K10) [16]	Dutch Health Monitor Public Health Services
		Public attitudes, stigma and taboo	Depression Stigma Scale [17]	Online Survey 113
			Attitude towards seeking professional psychological help short form [18]	Online Survey 113
			Questions on suicide experiences and perceived taboo	Online Survey 113
		Help-seeking behaviour	Change in monthly crisis calls to 113 during intervention compared with previous year	113
Part 2	Community facilitators	Identification of people with suicidal thoughts and linking to professional care	Number of people screened and linked to professional care in previous month	113
		Attitude and confidence	Questions on attitude toward suicide and confidence in assessing and managing suicidal patients	113
	General Practitioners	Identification of patients with depressive symptoms and suicide(attempt) in primary care	Change in recognition of depression and suicidal behaviour within primary care	NIVEL/Primary Care Database Sentinel Practices
		Compliance to professional standards and guidelines regarding the exploration of suicidal behaviour with patients presenting with depressive symptoms	Questions on the exploration of suicidal behaviour and what actions/interventions were proposed/agreed upon. The questions are added in Appendix A.	NIVEL/Primary Care Database Sentinel Practices

## Appendix A. Suicide Prevention within Primary Care-Scale

Q1 You registered a patient with a depressive disorder (ICPC 76). Is this a new episode?
  ❍ Yes
  ❍ No
Q2 Did you ask the patient if he/she had suicidal thoughts?
  ❍ Yes(GO TO Q3)
  ❍ No (GO TO Q16)
Q3 What did the patient answer?
  ❍ Yes, frequently, (WHEN NO NEW EPISODE (Q1 = NO), GO TO Q6)
  ❍ Yes, sometimes (WHEN NO NEW EPISODE (Q1 = NO), GO TO Q6)
  ❍ No ((WHEN NO NEW EPISODE (Q1 = NO), GO TO Q16, WHEN NEW EPISODE GO TO Q4–Q9, AND THEN TO Q16)
Q4 Do you know if the patient has a history of suicidal thoughts or behaviour?
  ❍ The patient has a history of suicidal thoughts or behaviour
  ❍ The patients has NO history of suicidal thoughts or behaviour
  ❍ I do not know that
Q5 Do you know if there is a family history of suicidal behaviour?
  ❍ There is a family history of suicidal behaviour
  ❍ There is NO family history of suicidal behaviour?
  ❍ I do not know that
Q6 Did you ask the patients if he/she lately has been worrying a lot about his/her problems and/or about dying?
  ❍ Yes, the patient has been worrying a lot about his/her problems and/or about dying
  ❍ No the patient has NOT been worrying a lot about his/her problems and/or about dying?
  ❍ I do not know that
Q7 Do you know if the patient experiences hopelessness?
  ❍ Yes, the patient experiences hopelessness
  ❍ No, the patient does not experience hopelessness
  ❍ I do not know that
Q8 Does the patient feel that he/she is a burden to others?
  ❍ Yes, the patient feels he/she is a burden to others
  ❍ No, the patient does NOT feel he/she is a burden to others
  ❍ I do not know that
Q9 Does the patient feel some kind of entrapment?
  ❍ Yes, the patient feels entrapped
  ❍ No, the patient does not feel entrapped
  ❍ I do not know that
Q10 Did you, or do you intend to involve significant others to discuss the patient’s suicidal thoughts?
  ❍ Yes
  ❍ No
Q11 Did you discuss with the patient how he/she can involve significant others to help the patient cope with his suicidal thoughts?
  ❍ Yes
  ❍ No
Q12 Do you know if there are recent stressors (lay-off, divorce) that might be related to the current suicidal thoughts?
  ❍ Yes, there are recent stressors (lay-off, divorce) that might be related to the current suicidal thoughts?
  ❍ No, there are NO recent stressors (lay-off, divorce) that might be related to the current suicidal thoughts?
  ❍ I do not know that
Q13 Do you know if the patient has made concrete plans/preparations (such as collecting medication, or buying a rope) to kill himself?
  ❍ Yes, the patient has made concrete plans/preparations to kill himself?
  ❍ No, the patient has made NO concrete plans/preparations to kill himself?
  ❍ I do not know that
Q14 Do you know if the patient trusts himself?
  ❍ Yes, the patient trusts himself
  ❍ No, the patient does NOT trust himself
  ❍ I do not know that
Q15 Did you feel confident enough to ask for suicidal thoughts?
  ❍ Yes
  ❍ No
Q16 Could you indicate why you did not ask for suicidal thoughts?
  ❍ I thought the patient would not be suicidal
  ❍ There was not enough rapport to ask such a sensitive question
  ❍ The patient indicated earlier that he was not suicidal
  ❍ I did not want to give the patient any ideas
  ❍ Different namely….. ____________________
Q17 Did you register the presence/absence of suicidal ideation?
  ❍ Yes, in the Electronic patient file
  ❍ No
  ❍ Yes, in the..... ____________________
Q18 Did you:
  ❍ Adopt a wait and see policy
  ❍ Make a follow-up appointment
  ❍ Refer the patient to a mental health nurse within primary care
  ❍ Refer the patient to specialized care
  ❍ Consult the crisis services, or a liaison psychiatrist?
  ❍ Prescribed antidepressants:
    (a) No
    (b) Benzodiazepine
    (c) Antidepressants
    (d) A combination of Benzodiazepine and antidepressants
  ❍ Recommended online help tools
  ❍ Made the patient aware of suicide crisis hotline
  ❍ Different, namely ____________________
Q19 When you referred a patient to specialized care, did you check if the patient indeed checked in?
  ❍ Yes
  ❍ No
  ❍ NA

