Furthermore, to measure change in guideline adherence, we will look at the key recommendation of the Dutch guidelines, i.e., the exploration of suicidal ideation and concrete suicide plans by GPs and/or primary care nurses [26,27] within the group of depressed patients. We will measure this by making use of a procedure similar to the one used within the sentinel practices of NIVEL Primary Care Database. Monthly, all new contacts for P76 (depressive disorder) within the electronic medical record of the intervention practices will be extracted by a research or doctor’s assistant. The GP or the mental health nurse will be asked to retrospectively answer an additional short questionnaire for each patient about whether or not suicidal thoughts have been explored, what was the level of intensity of the thoughts and concreteness of suicidal plans, and what actions/interventions were proposed/agreed upon. The questionnaire has been developed by experts and based on the recommendations of the Dutch suicide prevention guideline [26], and are added in supplement 1. These are basic elements of the gatekeeper training offered to GPs and mental health nurses in the SUPRANET communities. We will compare the answers of the intervention practices with data collected within a non-randomized group of 40 sentinel practices, a nationally representative subgroup of practices participating in NIVEL Primary Care database with in total 120,000 registered patients (0.7% of the Dutch population). Via these sentinel practices, NIVEL will collect additional data on suicide and suicide attempts over the last 30 years. In these practices an electronic tool incorporated in the EMD of the GP, the P-module, asks for additional information from the GP triggered by the use of an ICPC code, in order to discriminate between cases and non-cases. If a case is defined, the application generates an additional electronic questionnaire about the characteristics of the patient and the content of the GP encounter. In the past 30 years such an additional questionnaire has been used in suicidal patients after fatal and non-fatal suicide attempts indicated by ICPC-code P77 used by the GPs [28]. For the present study a new category has been defined with an extension of the P-module and an extra electronic questionnaire related to TCPC code P76.

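### The printed skips in the GP questionnaire (Appendix A) send GPs who did ask to the item on why they did not ask, and collect confidence (Q15) only where the GP asked and the patient confirmed suicidal thoughts

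*Protocol article*

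**What the plan says.** Appendix A prints explicit skip instructions.

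- **Q2** (did the GP ask about suicidal thoughts): Yes leads to Q3, No leads to Q16.
- **Q3** (the patient's answer), denial: "No ((WHEN NO NEW EPISODE (Q1 = NO), GO TO Q16" if the episode is not new, and "WHEN NEW EPISODE GO TO Q4–Q9, AND THEN TO Q16" if it is.
- **Q3**, confirmation: for an episode that is not new the skip is to Q6, as in "Yes, sometimes (WHEN NO NEW EPISODE (Q1 = NO), GO TO Q6". For a new episode no skip is printed, so Q4 follows.
- **Q15**: "Did you feel confident enough to ask for suicidal thoughts". No skip is printed after it.
- **Q16**: "Could you indicate why you did not ask for suicidal thoughts". Its options are reasons for not asking plus free text. None of them lets the GP say that the question was asked.

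Section 3.3.4 uses the questionnaire to measure guideline adherence: it asks "about whether or not suicidal thoughts have been explored", how intense the thoughts and how concrete the plans were, and what action followed. Answers from intervention practices are compared with those from 40 sentinel practices. The stated hypothesis is that exploration becomes more frequent after training. Table 1 names Appendix A as the measurement for GP compliance.

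**The concern.** A GP who reaches Q3 has already recorded that the question was asked. Sending that GP to Q16 contradicts the answer just given. The resulting entry may look plausible: one Q16 option says that the patient had earlier indicated not being suicidal, and a GP who asked and got a denial could well tick it. Without reference to Q2 the error would not show.

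The second fault is one of omission. Q15 lies between Q14 and Q16, and both routes that jump to Q16 pass over it. Confidence is therefore not recorded for patients who were not asked, the group in which low confidence might explain the omission. Q16 lists no reason about confidence, so it could surface there only as free text. Any comparison of Q15 between practices or periods would also be made among respondents selected on asking, which is the behaviour the training aims to change.

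**Working it through.** **Step 1: trace every route.** Follow the printed skips, and take the next item in order where none is printed. Q1 has two values (new episode or not). Each combines with four outcomes: Q2 = No, or Q2 = Yes with Q3 = No, sometimes or frequently. That gives 8 routes.

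| Outcome | Routes | Q15 reached | Q16 reached | Q16 applies |
|---|---|---|---|---|
| Q2 = No | 2 | 0 | 2 | 2 |
| Q2 = Yes, Q3 = No | 2 | 0 | 2 (explicit skip) | 0 |
| Q2 = Yes, Q3 = sometimes or frequently | 4 | 4 | 4 (no skip after Q15) | 0 |
| Total | 8 | 4 | 8 | 2 |

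Q16 is reached on 8 of 8 routes and applies on 2. Of the 6 where it does not apply, 2 follow from an explicit instruction and 4 only from the absence of a printed jump. Q15 is reached on 4 of 8 routes, all of them asked and confirmed. Q2 comes before every faulty skip, and Q17 to Q19 are reached on every route.

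**Step 2: the share of Q16 records to filter out.** The protocol gives neither the proportion of patients asked (a) nor the proportion of those who answer yes (y), so both are assumptions. Counting only the explicit Q3 = No skip, the share of Q16 records from GPs who did ask is

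a(1 − y) / [a(1 − y) + (1 − a)].

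- Low end, a = 0.5, y = 0.4: 0.30 / (0.30 + 0.50) = 0.375, about 38%.
- Middle, a = 0.7, y = 0.3: 0.49 / (0.49 + 0.30) = 0.62.
- High end, a = 0.8, y = 0.2: 0.64 / (0.64 + 0.20) = 0.76.

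If the run-on from Q15 also occurs, everyone reaches Q16 and the share is simply a, that is 50–80%.

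**Step 3: the share depends on the asking rate.** With y held at 0.3:

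- a = 0.5: 0.35 / 0.85 = 41%
- a = 0.7: 0.49 / 0.79 = 62%
- a = 0.8: 0.56 / 0.76 = 74%

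If training raises asking as hypothesised, unfiltered Q16 distributions would differ between groups through routing alone.

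**Step 4: coverage of Q15.** Q15 is answered for a × y of patients: 0.5 × 0.2 = 10% at the low end, 0.7 × 0.3 = 21% in the middle, 0.8 × 0.4 = 32% at the high end. It is answered for 0% of patients who were not asked.

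**The case against.** The strongest reply is that little of what the plan sets out to test depends on these two items. Section 3.3.4 and Table 1 define the GP outcome as exploration of suicidal behaviour and the actions taken. They do not name reasons for not asking or GP confidence. In Table 1, attitude and confidence belong to the community facilitators, who have a separate instrument (Section 3.3.3). That stands, and it rules out several stronger readings that a reader might infer:

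- **That the adherence outcome is compromised.** It is not. Q2 precedes every faulty skip, and the hypothesis on exploration rests on Q2.
- **That the Q16 data are invalid beyond repair.** They are not. Q2 is recorded on every questionnaire, so restricting Q16 to Q2 = No keeps every legitimate reason. The percentages in the working are a share of records to discard, not a bias in a planned estimate.
- **That Q15 will almost always be answered Yes and so cannot show a training effect.** The protocol gives no basis for this. A GP can ask without feeling confident, and no comparison of Q15 is described.
- **That every GP whose patient said yes is certainly sent to Q16.** This is inferred from a missing jump in a printed appendix. Sentinel practices use an electronic form, which may be routed differently, though the article does not say so.

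The reply does not answer the explicit Q3 = No instruction, nor the explicit Q2 = No skip past Q15. Free text at Q16 could capture some lack of confidence, but not systematically.

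**Conclusion.** The printed routing is wrong for two supporting items. The explicit skips put the why-not item to GPs who asked and received a denial. GPs whose patient confirmed suicidal thoughts appear to run on into the same item. Confidence to ask is collected only for patients who were asked and confirmed.

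The consequence is limited. The Q16 problem can be repaired by a filter on Q2. The Q15 gap cannot be repaired afterwards, and any comparison of Q15 between groups or periods would be selected on asking. The 38–76% of Q16 records to filter out, and the 10–32% coverage of Q15, rest on assumed asking and yes rates of 50–80% and 20–40%. The routing fault itself rests on no assumption apart from the inferred run-on after Q15.

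**What to change.** Correct the skips identically in intervention and sentinel practices:

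- Q2 = No → Q15 → Q16 → Q17.
- Q3 = No → Q4 to Q9 if the episode is new → Q15 → Q17.
- Q3 = Yes → Q4 (new episode) or Q6 (not new) through Q15 → Q17.

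Check the live electronic form against this routing. State that Q16 is analysed only where Q2 = No, and set it to missing on completed questionnaires with Q2 = Yes. Treat Q15 from questionnaires already completed as descriptive of asked-and-confirmed patients only.

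The cost is an edit to the skip logic. No item is added, although Q15 is put to more respondents. Q15 answers not collected before the change stay lost, so the edit is worth making early.

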#### 2.2.4. Component 4: Training and Support in General Practice

SUPRANET has a strong focus on change in recognition and treatment of suicidal behaviour in Dutch primary care. Therefore, crucial to each community, is the participation of general practice, notably the general practitioners (GPs) and their mental health support staff (POH). This is a relatively new professional in most Dutch general practices, most often with a nursing or psychological background, providing brief coaching sessions to patients after being diagnosed by the GP. We aim to recruit at least five GP practices within each region. As part of the intervention, a suicide prevention training package is offered to primary care staff in 2017–2018, stimulating the exploration of suicidal ideation and concrete suicide plans among patients. In addition, the practices will work on continuity of care by improving collaboration with social community teams, emergency rooms, and mental health care.

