We hypothesize that, within the intervention practices, suicide ideation will be more often explored within depressed patients after the suicide prevention training offered to primary care staff (2017–2018) as part of the intervention, when compared to the period before the training (2016) and when compared to those sentinel practices who are not part of the intervention group and did not have the training.

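### Exploring concrete suicide plans is a named part of the guideline-adherence outcome, but Appendix A records only what the clinician knows about plans (Q13), not whether the clinician asked

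*Protocol article*

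**What the plan says.** - **Outcome.** Protocol article, section 3.3.4, measures change in guideline adherence through one key recommendation: "the exploration of suicidal ideation and concrete suicide plans by GPs and/or primary care nurses". Two acts by the clinician are named.
- **Training target.** Section 2.2.4 describes the training package as "stimulating the exploration of suicidal ideation and concrete suicide plans among patients", so both acts are also what the training is meant to change.
- **Measure.** Table 1 gives the measurement as "Questions on the exploration of suicidal behaviour and what actions/interventions were proposed/agreed upon" and points to Appendix A. Section 3.3.4 describes the questionnaire as covering "whether or not suicidal thoughts have been explored, what was the level of intensity of the thoughts and concreteness of suicidal plans".
- **Hypothesis.** The directional statement closing section 3.3.4 is that "suicide ideation will be more often explored within depressed patients after the suicide prevention training offered to primary care staff". It names ideation only.
- **Items.** Q2 asks whether the clinician asked about suicidal thoughts (yes/no), and Q3 records the patient's answer. The only plans item is Q13, "Do you know if the patient has made concrete plans/preparations", with three options: the patient has plans, the patient has none, or the clinician does not know. Q2 = No goes straight to Q16. Q3 = No also bypasses Q13, in new and existing episodes alike.

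**The concern.** An outcome defined as exploration needs an item that records exploration. For thoughts the form has one. For plans it asks about the clinician's state of knowledge, and that can come from asking, from other information or from assumption. The form is completed retrospectively, after a monthly extraction of records, which leaves room for inference.

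At stake is the plans component of the adherence outcome. If training moves clinicians from assuming there are no plans to asking and hearing that there are none, Q13 does not change. Because the act is never recorded, no scoring rule written later can recover it. This is therefore not a detail that an analysis plan could supply.

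**Working it through.** The plan gives no figure for this outcome, so there is nothing to reproduce. The check is of wording and routing, followed by an illustration with assumed inputs.

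**1. Outcome against items**

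| Component named in section 3.3.4 | Item recording the act | Item recording the content |
|---|---|---|
| Ideation | Q2 (yes/no) | Q3 |
| Concrete plans | none in Q1–Q19 | Q13 |

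**2. What a Q13 answer can mean.** Q13 is reached only with Q2 = Yes and Q3 = frequently or sometimes. Within that group:

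- Asked and told no, or did not ask and assumed no: both tick 'no plans'.
- Asked with no clear answer, or did not ask and made no assumption: both tick the don't-know option.

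**3. Dilution.** The natural proxy for exploration is a definite answer (has plans or has none). Let *a* be the share of patients reaching Q13 in whom plans were asked about, *d* the chance that asking gives a definite answer, and *s* the chance that a clinician who did not ask still ticks a definite answer. Then

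P(definite) = *a·d* + (1 − *a*)·*s*

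and, if *d* and *s* are the same in both groups or periods, a true rise from *a*₀ to *a*₁ appears as (*a*₁ − *a*₀)(*d* − *s*).

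The article gives none of these inputs. Assume *a* rises from 0.50 to 0.80, a true gain of 30 points:

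| *s* | *d* = 1: 30 × (1 − *s*) | *d* = 0.95: 30 × (0.95 − *s*) |
|---|---|---|
| 0 | 30 | 28.5 |
| 0.25 | 22.5 | 21 |
| 0.50 | 15 | 13.5 |
| 0.75 | 7.5 | 6 |
| 1 | 0 | −1.5 |

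With *d* = 1 the share of the effect lost equals *s*: nothing if non-askers always admit they do not know, everything if they always assume.

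**4. If *s* differs between the groups.** With *d* = 1:

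- *s*₀ = 0.75 and *s*₁ = 0.25: (0.80 + 0.20 × 0.25) − (0.50 + 0.50 × 0.75) = 0.850 − 0.875 = −2.5 points.
- *s*₀ = 0.10 and *s*₁ = 0.50: (0.80 + 0.20 × 0.50) − (0.50 + 0.50 × 0.10) = 0.90 − 0.55 = 35 points.

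Dilution towards no effect is therefore the result under equal *s*, not a certainty.

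**5. Who reaches Q13.** Training is expected to raise Q2 and so to change which patients get as far as Q13. Assume thoughts asked about / disclosed if asked / plans explored if disclosed of 80/30/70% in trained and 50/40/80% in comparison practices. Per 100 P76 patients:

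| | Trained | Comparison |
|---|---|---|
| Thoughts not asked about | 20 | 50 |
| Asked, thoughts denied | 80 × 0.7 = 56 | 50 × 0.6 = 30 |
| Disclosed, plans explored | 80 × 0.3 × 0.7 = 16.8 | 50 × 0.4 × 0.8 = 16.0 |
| Disclosed, plans not explored | 80 × 0.3 × 0.3 = 7.2 | 50 × 0.4 × 0.2 = 4.0 |

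Among disclosers the trained practices look worse (70 v 80%); per P76 patient they are slightly ahead (16.8 v 16.0%). The second figure is no cleaner, because it counts the 56 and 30 who denied thoughts as if plans had gone unexplored. Neither denominator is enough alone.

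**The case against.** The strongest defence is that the only directional hypothesis concerns exploration of ideation, which Q2 measures as an act in every P76 patient. The description of the questionnaire promises exploration for thoughts and, for plans, their concreteness, which Q13 largely delivers. **This stands as a limit on scope.** A reader might infer that half of the outcome is lost, or that the guideline-adherence comparison fails. The documents support neither: they give the two components no weights, and the ideation comparison is intact. But the adherence outcome and the training target both name exploration of plans, and the defence does not supply an item for it.

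Second, Q13 is not blind. It offers a don't-know option, and its routing confines the ambiguity to clinicians who asked about thoughts and heard yes. **Both points stand.** They make Q13 an imperfect proxy, not a useless one.

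Third, the size is assumed. **This stands.** A reader might take a loss of 30% to 80% (the *d* = 0.95 column at *s* = 0.25 to 0.75) as an estimate. It is not, and at *s* = 0 the same formula loses only 5%.

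Fourth, the article states no denominator or scoring rule for Q13. **This also stands.** A reader might infer that the plan commits itself to comparing patients selected by the training; it does not say so. The selection issue bears on how a corrected item should be reported and is not itself an error in the plan.

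Two neighbouring items might be read as further evidence, but neither is. Q6, "Did you ask the patients if he/she lately has been worrying a lot about his/her problems and/or about dying", is not about plans and does have an asking stem; its separate, smaller fault is that no answer option says the question was not asked. The article also promises "what was the level of intensity of the thoughts and concreteness of suicidal plans", whereas Q3 grades only frequency. That is loose wording on which no stated comparison depends.

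**Conclusion.** The point holds in limited form. Exploration of concrete plans is named as part of guideline adherence and as a training target, but Appendix A does not record it as an act. Among patients who disclosed ideation, Q13 cannot separate asking from assuming, or asking without a clear answer from not asking.

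If non-askers in the groups compared are equally likely to give a definite answer, a training effect on plan exploration is diluted by an unknown amount: none when they always tick don't know (and asking always settles the matter), more as more of them assume. If that likelihood differs between groups, the distortion can go either way. The figures above show direction and range only.

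**What to change.** 1. Before Q13, add a yes/no item: 'Did you ask about concrete plans/preparations?' Use identical wording in the intervention-practice form and in the P-module of the sentinel practices.
2. Keep Q13 for content and add a 'no clear answer' option. Score plan exploration from the new item.
3. Report it among patients who disclosed ideation and also as a share of all P76 patients, showing those who denied thoughts as a separate category and not as 'not explored'. Both are needed because training is expected to change who reaches Q13.
4. Give Q6 answer options that match its asking stem.
5. If the form can no longer be changed, restrict the stated adherence outcome to exploration of ideation and describe Q13 as clinician knowledge of plans.

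**Cost:** one extra tick per patient, small edits to the form and the module, and a sentence on scoring. Section 3.3.4 compares with the period before training (2016) and describes the module extension as already defined. Where forms are already in use, the new item has no pre-training baseline, so the existing Q13 answers must be kept for the before–after comparison and the new item used for the comparison between practices.
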